##### Face-to-face group intervention

The face-to-face group intervention includes six group coaching meetings (Table 3) organized in local health care centers. The groups are facilitated by nurses and other health-care professionals who have received a 2-day training program following the principles of strength-based behavioral coaching. This approach has been designed and tested in the GOAL lifestyle intervention [12, 34] and further developed in several other studies in Finland and other countries [35].

**Table 3 Tab3:** Contents of the StopDia face-to-face group meetings

Meeting topics	Key points
1. Orientation to the StopDia group coaching	Get familiar with other participants and the program Information on type 2 diabetes and lifestyle factors in its prevention
2. Rhythm of daily life	Observation of the daily rhythms of eating habits, physical activity, sedentary behavior, stress, sleeping, and rest Tools for management of daily life Goal setting and planning: Actionable behavioral goals to improve rhythm of daily life
3. Let’s eat well and healthy	Self-monitoring and reflection of dietary habits Principles of a healthy diet Goal setting and planning: Actionable behavioral goals for diet
4. Enjoying physical activity	Self-monitoring and reflection of physical activity Principles of sufficient physical activity Goal setting and planning: Actionable behavioral goals for physical activity
5. Automating activity to everyday life	How can I nudge myself to healthy lifestyle? Goal setting and planning: Actionable behavioral goals for re-designing home environment to support healthy choices
6. Succeeding in lifestyle management, also after the StopDia study	Self-evaluating program outcomes Learning and insights for future Planning for maintenance of behavior changes

Group meetings 1–5 are planned to be fortnightly and group meeting 6 approximately one month after meeting 5

All nurses receive the StopDia Instructors Manual where the contents of each group meeting are described with participatory activities and lead questions. The participants receive the StopDia Participant Workbook. The duration of the group coaching program is 3–4 months, and there are 6–15 participants in each group. Each meeting contains 90 min of organized activity and 30 min of optional activity. All meetings follow a similar enabling and functional structure supporting participant autonomy and participatory action that includes 1) warm-up to the meeting topic; 2) identification of strengths of the participants, including former knowledge, skills, and healthy lifestyle habits related to the topic; 3) learning something new and getting ideas for lifestyle change; 4) formulation of behavioral goals and action planning; 5) identification of sources of support and help needed to carry out the plan; and 6) closing the meeting with commitment to action. Between the face-to-face meetings, lifestyle changes are supported by homework materials and tools, available in the StopDia Participant Workbook. The nurses report the realization of the group coaching by filling out a detailed questionnaire after every group meeting.

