#### Examination visits and randomization

Individuals identified to be eligible by the StopDia Digital Screening Tool are automatically invited to participate in the randomized controlled trial. On the StopDia webpages, an individual who is willing to participate is given instructions on how to contact a nurse in a local health care center for examination visits.

At the first examination visit, the participant signs an informed consent, and the nurse measures body weight, body height, waist circumference, and blood pressure using calibrated devices, makes a referral to the laboratory measurements, and gives a blood sampling kit and tubes to the participant for the laboratory measurements. The sampling kit and the tubes are identified with numerical identification codes. After the first examination visit, the participant receives a personal link by email to a web-based StopDia Digital Questionnaire developed using the LimeSurvey platform (LimeSurvey GmbH, Hamburg, Germany). The participant is instructed to complete the questionnaire within two weeks.

The second examination visit is carried out in the laboratory of the local health care center. The participant is instructed to fast for 12 h, avoid strenuous physical activity, abstain from drinking alcohol for 24 h, and avoid smoking in the morning before the visit. Trained laboratory nurses take fasting blood samples for routine laboratory tests, explained in detail in Assessments, and blood samples during the 2-h OGTTs. These blood samples are stored and analysed at local clinical laboratories. Additional blood samples for research purposes, taken with a sampling kit, are frozen and transported to the laboratory of the StopDia research group at the University of Eastern Finland.

The participants who meet the inclusion criteria and have no exclusion criteria according to the StopDia Digital Screening Tool, have filled out the StopDia Digital Questionnaire, have given blood samples, and have no type 2 diabetes according to the results of the 2-h OGTT are randomly assigned into one of the three study groups (digital lifestyle intervention, digital and face-to-face group lifestyle intervention, control) with 1:1:1 allocation using a computerized randomization system. Individuals whose 2-h OGTT indicates the diagnosis of type 2 diabetes are directed to diabetes care following the normal principles of the provinces.

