#### Power and sample size calculation

The estimation of the number of individuals needed in the randomized controlled trial is based on power calculations relying on the net difference of 0.6 mmol/l in the change of 2-h plasma glucose during the first 12 months of follow-up between the intensive lifestyle intervention group and the control group in the Finnish Diabetes Prevention Study [1]. Due to the real-life community-based approach in the StopDia study, we realistically anticipate achieving about 0.3 mmol/l net difference in the change of 2-h plasma glucose during the 12-month follow-up between the intervention group and the control group. We estimate that a minimum number of participants required to detect an effect size of at least 0.2 mmol/l in the change of 2-h plasma glucose concentration with a power of 80% (*p* = 0.05, allowing for a 10% loss to follow-up or missing data) is 1000 participants in each group.

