#### Statistical analyses

The statistical analyses will be performed following the CONSORT 2010 statement guidelines for randomized controlled trials. The effects of the intervention on the primary and secondary outcomes during follow-up are analysed using the intention-to-treat principle. Linear mixed effects models adjusted for relevant confounding factors are used to analyse the effects of the interventions on the outcomes. Appropriate correction methods are used to reduce the likelihood of false positive findings in the statistical analyses. Differences in variables between the groups and associations and interactions between variables with *p*-values of < 0.05 are considered statistically significant. Most of the statistical analyses are performed using the IBM SPSS Statistics® software (IBM Corp., Armonk, NY, USA), but the SAS and R software may also be used.

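### One arm is coached in shared groups of 6–15, but the sample size lists no clustering allowance and the mixed model is described without a coaching-group term

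*Protocol article*

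**What the plan says.** All places are in the Protocol article.

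- **Allocation** (Examination visits and randomization): individuals are assigned to three arms "with 1:1:1 allocation using a computerized randomization system".
- **Delivery** (Face-to-face group intervention): one arm adds six coaching meetings at local health care centers, led by nurses and other professionals. The programme lasts 3–4 months, "and there are 6–15 participants in each group". The digital-only and control arms have no such groups.
- **Sample size** (Power and sample size calculation): the minimum number "to detect an effect size of at least 0.2 mmol/l in the change of 2-h plasma glucose concentration with a power of 80" per cent, at p = 0.05 and "allowing for a 10% loss to follow-up or missing data", "is 1000 participants in each group". Here the last word means a study arm. The same paragraph says "we realistically anticipate achieving about 0.3 mmol/l net difference in the change of 2-h plasma glucose". It gives no standard deviation, ICC or design effect.
- **Model** (Statistical analyses): "Linear mixed effects models adjusted for relevant confounding factors are used to analyse the effects of the interventions on the outcomes". No random effect of any kind is named.

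**The concern.** This is a partially nested design: allocation is by individual, but after randomisation one arm is gathered into clusters that share a facilitator, peers and sessions. The article gives reasons to expect some correlation within a group. Its theoretical background stresses social relatedness, the first meeting is meant to acquaint members with one another, and every meeting is participatory and ends with commitments.

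Positive correlation raises the variance of that arm's mean. Two contrasts inherit this: face-to-face against control, and face-to-face against digital only. The second shows whether coaching adds anything to the app. Two things are at stake: whether the quoted 80% power holds for these contrasts and, if the fitted model has no group term, whether their confidence intervals and p-values are valid. The issue applies to all five primary outcomes in Table 4, although the sample size concerns only 2-h glucose.

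**Working it through.** **Inputs from the article.** Difference 0.2 mmol/l (anticipated 0.3), power 80%, alpha 0.05, 1000 per arm, 10% loss, coaching groups of 6–15. Two-sided testing is assumed, since sidedness is not stated.

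**Assumed.** ICC 0.01, 0.02 and 0.05. The article gives none.

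**Step 1: the plan's own figure.** It cannot be reproduced forwards, because no SD of the change is given. Solving backwards with 1000 × 0.9 = 900 evaluable per arm and independent participants:

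SD = 0.2 / (1.960 + 0.842) × √(900/2) = 1.51 mmol/l.

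This SD returns 900, and 900/0.9 = 1000, by construction. It is a consistency check and not evidence of how the figure was obtained.

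**Step 2: effect of clustering in one arm.** With group size m, the design effect in the face-to-face arm is DE = 1 + (m − 1) × ICC. The other arm of the contrast keeps a design effect of 1. The true standard error relative to the independent one is

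R = √((1 + DE)/2).

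If 1000 per arm gives 80% power under independence, the difference of 0.2 equals 2.80 standard errors, so the SD is not needed:

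- power at 0.2 = Φ(2.80/R − 1.96)
- power at 0.3 = Φ(1.5 × 2.80/R − 1.96)
- type I error if clustering is ignored = 2 × (1 − Φ(1.96/R))

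| m | ICC | DE | R | Power at 0.2 | Power at 0.3 | Type I error if ignored |
|---|---|---|---|---|---|---|
| any | 0 | 1.00 | 1.000 | 80.0% | 98.8% | 5.0% |
| 6 | 0.01 | 1.05 | 1.012 | 79.0% | 98.6% | 5.3% |
| 6 | 0.02 | 1.10 | 1.025 | 78.1% | 98.4% | 5.6% |
| 6 | 0.05 | 1.25 | 1.061 | 75.2% | 97.7% | 6.5% |
| 10.5 | 0.01 | 1.095 | 1.023 | 78.2% | 98.4% | 5.5% |
| 10.5 | 0.02 | 1.19 | 1.046 | 76.3% | 98.0% | 6.1% |
| 10.5 | 0.05 | 1.475 | 1.112 | 71.2% | 96.5% | 7.8% |
| 15 | 0.01 | 1.14 | 1.034 | 77.3% | 98.2% | 5.8% |
| 15 | 0.02 | 1.28 | 1.068 | 74.7% | 97.6% | 6.6% |
| 15 | 0.05 | 1.70 | 1.162 | 67.4% | 95.1% | 9.2% |

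Worked case, m = 15 and ICC 0.05: DE = 1 + 14 × 0.05 = 1.70; R = √(2.70/2) = 1.162; 2.80/1.162 − 1.96 = 0.45; Φ(0.45) = 0.67.

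**Step 3: the same result on other scales.** The true standard error is 1% to 16% larger than the independent one. A model that ignores clustering therefore reports one that is 1 − 1/1.012 = 1% to 1 − 1/1.162 = 14% too small. The difference detectable with 80% power moves from 0.20 to between 0.202 and 0.232 mmol/l. Restoring 80% at 0.2 with equal arms would take about 1026 to 1352 per arm including the 10% loss.

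**Step 4: sensitivity to attrition.** If the 10% loss also thins each group, 15 becomes 13.5. Then DE = 1 + 12.5 × 0.05 = 1.625, R = √(2.625/2) = 1.146, and power at 0.2 is Φ(2.80/1.146 − 1.96) = Φ(0.49), about 69%. The worst case softens slightly and the conclusion does not change.

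**The case against.** **The model is not shown to ignore the groups.** A reader might infer from the silence on coaching groups that the analysis treats participants as independent. The article does not support that. It names a mixed model without its random effects, and that detail is commonly left to an analysis plan or full protocol, neither of which is shown. This stands, so the standard error and type I error figures are conditional on no group term being fitted. The words mixed model do not settle the matter either, because a model with only a participant effect would leave the problem in place.

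**The back-solved SD proves nothing.** A reader might take the match at SD 1.51 as proof that no design effect was used. It is circular. A design effect of 1.18 with SD 1.514/1.044 = 1.45, or of 1.45 with SD 1.514/1.107 = 1.37, would also give 1000. This stands. What remains is that the paragraph lists its allowances, clustering is not among them, and the clustered arm receives the same number as the others.

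**The ICC is assumed and there is a reserve.** The mildest case costs one point of power. The worst needs every group at the maximum size together with the highest ICC assumed. At the anticipated 0.3 mmol/l, power is at least 95% throughout. This stands and limits the power complaint to the stated 0.2 mmol/l target. It does not help with type I error, which does not depend on the effect size.

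**No ranking of arms is stated.** A reader might also suppose that the face-to-face arm is the one most likely to be declared effective, which would make the problem more pressing. The article says nothing of the kind.

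**Conclusion.** The point holds in a conditional form. The article sets out individual randomisation with group delivery in one arm only, lists no clustering allowance, and does not say whether coaching group enters the model.

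Whenever the within-group ICC exceeds zero, the stated 80% at 0.2 mmol/l is too high for face-to-face against control. It is equally too high for face-to-face against digital only at the same difference, although the sample size paragraph frames its difference as intervention against control. Over the assumed ICC of 0.01–0.05 and the stated group sizes, power is about 79% to 67%. If in addition no group term is fitted, standard errors for the two contrasts are about 1% to 14% too small and type I error is about 5.3% to 9.2%.

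Digital-only against control is untouched by this clustering. The calculations rest on two-sided testing, equal group sizes and everyone in the arm belonging to one group (1000/15 = 67 to 1000/6 = 167 groups).

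**What to change.** 1. **Record the coaching group to which each participant is assigned**, and carry that identifier into the analysis file. Define the cluster by assignment and not by attendance, to stay within intention-to-treat.
2. **Specify a partially nested mixed model** for the contrasts with the face-to-face arm: a random intercept for coaching group in that arm only, participants in the other arms as singletons, arm-specific residual variance, and Satterthwaite or Kenward-Roger degrees of freedom.
3. **Restate power** for the two contrasts at 0.2 and 0.3 mmol/l over a stated range of ICC, and give the SD used. Recruitment need not change.

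The cost is a slightly wider confidence interval for that arm and one more data item. The data item needs confirming now. The article describes a questionnaire that nurses complete after each meeting, and facilitator logs, but does not say that participant-level group membership is kept. It could be hard to reconstruct later. If the analysis plan already contains the group term, only the power statement needs changing.

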##### Control group

The control group receives a digital information package on lifestyle risk factors for type 2 diabetes and dietary and physical activity recommendations to decrease the risk of type 2 diabetes. They are also informed that they will have the opportunity to use the BitHabit application after the one-year follow-up.

#### Primary and secondary outcomes

The primary and secondary outcomes of the randomized controlled trial are changes in the corresponding variables during the 1-year follow-up listed in Table 4. Each of them are described in more detail in the following paragraphs.

**Table 4 Tab4:** The primary and secondary outcomes of the randomized controlled trial

Primary outcomes	Secondary outcomes (in more detail below and in ClinicalTials.gov. Identifier: NCT03156478)
Body weight	Waist circumference
Fasting plasma glucose	Serum insulin and plasma lipids
Two-hour plasma glucose from OGTT	Systolic and diastolic blood pressure
Dietary score	Sedentary behavior
Total physical activity	Psychosocial factors and mental wellbeing Use of health and social care and associated costs

#### Assessments based on StopDia digital questionnaire at baseline and one-year follow-up

##### Sociodemographic factors

Date of birth, gender, marital status, education, employment status, the number of household members, household income, economic problems during the last 12 months, and ethnic origin are asked.

##### History of diseases and use of medications and health care services

Perceived health, the perceived risk of developing type 2 diabetes, the history of 32 non-communicable diseases diagnosed by a physician, the lifetime history of weight loss, perceived memory, adopting new knowledge, learning new things, the family history of type 1 and 2 diabetes, coronary heart disease, ischemic stroke, hemorrhagic stroke, hypertension, obesity, and dementia diagnosed by a physician, and diseases reimbursed by the social security system are asked. The use of health care services and prescribed medications during the last 12 months are also inquired.

##### Food, drink, and alcohol consumption and eating behavior

Food, drink, and alcohol consumption is assessed by 18 items that are slightly modified from a previously validated Finnish food intake questionnaire [36]. A composite diet quality score is created to reflect the goals of the intervention. The features of eating behavior are assessed using items from the ecSatter Eating Competence Inventory 2.0 (ecSI 2.0) [37] and the Three Factor Eating Questionnaire (TFEQ-R18, emotional eating factor) [38].

##### Physical activity and sedentary behavior

Conditioning physical activity, everyday physical activity, physical activity to and from work, physical activity and sitting at work, and sitting and other sedentary behavior during leisure time are assessed using questions modified from those of the Finrisk study [39, 40] and the Kuopio Ischaemic Heart Disease Risk Factor study [41] in Finland and the International Physical Activity Questionnaire [42].

##### Sleep behavior, smoking, and alcohol consumption

Sleep behavior, including duration, quality, timing, and regularity, is assessed by questions modified from the Basic Nordic Sleep Questionnaire [43]. Smoking habits are assessed using questions modified from the Finrisk 2012 survey [44]. Alcohol consumption is assessed by items modified from a previously validated Finnish food intake questionnaire [36].

##### Psychosocial factors

Motivation to eat healthy and do physical activity is assessed by the four best items of autonomous motivation and the four best items of controlled motivation from the Treatment Self-regulation Questionnaire [45]. We added two items of intrinsic motivation. Perceived competence is assessed by the Nutrition Self-Efficacy Questionnaire and the Physical Activity Self-Efficacy Questionnaire [46]. Self-regulation is assessed by the Brief Self-Control Scale [47], action and coping planning by items modified from the Action and Coping Planning Scales (only at one-year follow-up) [48], behavioral automaticity by the automaticity subscale from the Self-Report Behavioural Automaticity Index (only at one-year follow-up) [49], social support for physical activity and diet with a modified version of the Brief Social Support Scale (only at one-year follow-up) [50], and time orientation by four items modified from the 22-item Zimbardo Time Perspective Inventory [51]. Quality of life is assessed by the World Health Organization Quality of Life scale [52] and work ability and activity by the Work Productivity and Activity Impairment Questionnaire [53]. Mental wellbeing is assessed by the Warwick-Edinburgh Mental Well-being Scale [54], satisfaction with life by the Cantril’s Self-Anchoring Ladder [55], perceived stress by the Perceived Stress Scale [56], and resilience by the 14-item Resilience Scale [57]. Loneliness is assessed by the 12-item version of the UCLA Loneliness Scale [58, 59]. Questions used to assess cognition, including perceived memory and learning capability, are from Finrisk 2012 survey [44]. The dementia risk score is computed based on a previously created risk score [60].

#### Measurement of anthropometrics and blood pressure

Height, weight, waist circumference, and blood pressure are measured by trained nurses in local health care centers. Body weight is measured in light indoor clothing by digital scales to accuracy of 0.1 kg. Body height is measured in a Frankfurt position and without shoes by scaled height meters to accuracy of 1 cm. Body mass index (BMI) is calculated by dividing body weight in kilograms by the square of body height in meters. Waist circumference is measured in a standing position on bare skin at the end of normal exhalation and at the mid-distance between the bottom of the rib cage and the top of the iliac crest to accuracy of 1 cm. Resting blood pressure is measured after a 5-min rest two times with 2 min intervals from the right arm in a sitting position with standard automatic sphygmomanometers to accuracy of 1 mmHg. The means of the two measurements are used as systolic and diastolic blood pressure.

#### Laboratory measurements

Blood samples for measuring glucose and insulin metabolism (fasting, 30-min, and 2-h glucose and insulin from 2-h OGTT), lipid metabolism (fasting plasma total, LDL, and HDL cholesterol and triglycerides), liver function (serum aspartate aminotransferase and alanine aminotransferase), biliary function (serum alkaline phosphatase), kidney function (serum creatinine), and thyroid function (serum thyreotropin) are analysed in the standardized quality-controlled clinical laboratories of the three provinces or in the laboratory of the University of Eastern Finland. The disposition index_30_ (DI_30_) is used as a surrogate measure of early-phase insulin secretion, and the Matsuda index of insulin sensitivity (Matsuda ISI) is used as a surrogate measure of peripheral insulin sensitivity, as previously validated against the 2-h OGTT [61–63]. Blood samples for genetic analyses and metabolite profiling will be analysed in the research laboratory of the University of Eastern Finland.

#### Assessment of the use of health care services and medications and health economic evaluation

The use of health care services in outpatient clinics of hospitals, public health care centers, occupational health care centers, and private health care providers as well as at home and the use of medications of the participants during the last 12 months are asked in a questionnaire. The use of health care services and medications and associated costs are also received from Care Register for Health Care (outpatient and inpatient visits in hospitals) and Register of Primary Health Care Visits (outpatient and inpatient visits in public health care centers) of National Institute for Health and Welfare of Finland and Finnish Prescription Register (reimbursed medicines) and other registers of Social Insurance Institution of Finland (other costs related to health care) using national personal identity codes. The long-term cost-effectiveness of the interventions is assessed using health econonomic modelling, which makes it possible to simulate the expected health outcomes, costs, and cost-effectiveness of the interventions in the long term based on the observed short-term changes in risk factors for type 2 diabetes. The results of the health economic modelling will be confirmed by the register-based cost-effectiveness analyses in the future.

